**Secondary outcomes**

1. *Number of lashes touching the eye at each visit.*

This will include data from all time points. We expect a large proportion of individuals with no lashes touching, and will thus use a random effects zero-inflated Poisson analysis (Lee et al, Statistical Methods in Medical Research 2006:15:47-61). This model is suitable for count data with an excess of zeros, and adjusts for within-patient correlation. The model will provide a coefficient, 95%CI and p-value for the difference in log mean number of lashes in the intervention versus control arms.

1. *Lashes touching the cornea:*

The number of lashes touching just the cornea will be compared between the two arms of the trial. Lashes that only touch the peripheral eyeball (i.e. the sclera rather than the cornea), are probably not of great visual or pathological significance. This will be analysed with similar methods to that for the total number of lashes touching the eye at each visit.

1. *Entropion grade*

The effect of the intervention on the degree of entropion at 24 months will be analysed by ordered logistic regression.

1. *Conjunctivilisation of the lid margin grade*

The effect of the intervention on the degree of conjunctivilisation at 24 months will be analysed by ordered logistic regression.

1. *Corneal opacification*
   1. Descriptive measures of the baseline severity of CO
   2. Description of the change in CO between baseline and one and two year follow up time-points.
   3. Ordinal logistic regression analysis for change in CO category at one year and two years respectively, to identify factors associated with it, such as inflammation.
   4. The effect of the intervention on the degree of change in CO between baseline and 24 months will be analysed by ordered logistic regression.
2. *Visual acuity*

The effect of the intervention on the visual acuity (logMAR score) at 12 and 24 months will be analysed by linear regression.

1. *Surgical complications and recurrence rate (in surgical arm)*

Surgical complications such as granuloma, incomplete lid closure, inflammation from suture material and infection can occur. The clinical status of the eyelid at the suture removal (7-10 days) will be described. The risk of complications in the surgical arm of the trial will be calculated at one year and two years respectively. The risk of recurrence (defined as at least one lash touching the eyeball or clinical evidence of epilation or redo surgery) will also be estimated at each visit.

1. *Patient satisfaction*

Patients are asked the following questions on the follow up questionnaires that indicate their satisfaction with the procedure:

- 1. *Do you think your vision is worse, the same or better than before your surgery or epilation?*
  2. *Do you have eye pain?*
  3. *If you have eye pain is it worse, the same or better than before your surgery or epilation?*
  4. *Do your eyes water?*
  5. *If you had surgery, did you find it painful?*
  6. *If you have been epilating do you find it painful?*
  7. *If you had surgery and the eyelashes have returned, do you want to have further surgery?*
  8. *If you have been epilating would you prefer to have had surgery?*

1. The answers to each of these questions will be compared between the two arms of the trial at 12 months. Additionally the answers to questions (b) and (d) will be adjusted for baseline (pre-operative) response.

Footnotes

1. *Why is corneal opacification not the primary outcome measure?*

Although corneal opacification is the outcome that is responsible for blindness (rather than trichiasis which is a risk factor for this) it can not be used as a primary measure for the following reasons:

1. As few as 10% of patients will have corneal opacity at the outset of the study.
2. The rate of change of corneal opacity can be slow, and the clinical examination is not sensitive enough to detect very subtle changes
3. Corneal opacity can be caused by other insults such as infection and trauma.
4. *Why is visual acuity not the primary outcome measure*

As with corneal opacity, loss of visual acuity is the end stage process from the disease. However it can not be used as a primary outcome measure because it is affected by many other common conditions such as cataract, as well as simply by aging.

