Trichiasis (lashes touching the eyeball) causes visual loss through corneal opacification. The purpose of the interventions being compared in this trial is to stop eyelashes touching the eyeball. It is anticipated that some of the patients in the surgery arm of the trial may commence epilation if their surgery fails. From an ophthalmic public health perspective they are ‘successes’ if they successfully prevent eyelashes touching the globe, despite the surgery itself having not been totally successful.

Previous studies have used a cut-off of 5 or more lashes for determining treatment choices (Arch Ophth 2006; 124: 309-314). Similarly, this level has been used in national blindness control programmes (The Gambia) as an indication for surgery.

*c) Sample size*

Our sample size of 1300 trial participants would provide 90% power to detect non-inferiority, assuming 10% loss to follow-up over 2 years, a 5% failure rate in the surgery arm, and non-inferiority margin of 10%. (i.e we would conclude non-inferiority if the upper 95%CI for the observed difference in failure rates was less than 10%)

The power to detect non-inferiority under different assumptions with this sample size is shown in the table below

**Table 1:** Power for detecting non-inferiority under different assumptions with sample size of 585 per arm (1300 recruited, 10% loss to follow-up)

| **Proportion failing in surgery arm (**[figure not shown] | **Proportion failing in epilation arm (**[figure not shown] | **Difference in proportions (**µ) | **Inferiority margin (**Δ) | **Power** |
| --- | --- | --- | --- | --- |
| 2% | 6% | 4% | 8% | 93% |
| 2% | 8% | 6% | 10% | 89% |
| 3% | 6% | 3% | 8% | 98% |
| 3% | 9% | 6% | 10% | 85% |
| 4% | 8% | 4% | 8% | 82% |
| 4% | 8% | 4% | 10% | 99% |
| 4% | 9% | 5% | 10% | 94% |
| 5% | 9% | 4% | 8% | 76% |
| **5%** | **10%** | **5%** | **10%** | **90%** |
| 8% | 11% | 3% | 8% | 83% |
| 8% | 12% | 4% | 10% | 93% |

*d) Statistical analysis*

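### The zero-inflated Poisson coefficient is the difference in log mean lash number only if zero inflation is equal in both arms, which the plan does not state or justify

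*Protocol*

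**What the plan says.** The Analytical Plan for Trial 2, which is part of the Protocol, lists the lash count at each visit first under "Secondary outcomes". It gives its reason for the model: "We expect a large proportion of individuals with no lashes touching". It then says that the analysis "will thus use a random effects zero-inflated Poisson analysis". On the data it says "This will include data from all time points", and on the result: "The model will provide a coefficient, 95%CI and p-value for the difference in log mean number of lashes in the intervention versus control arms".

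The next item, lashes touching the cornea, follows the same route: "This will be analysed with similar methods to that for the total number of lashes touching the eye at each visit".

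The text does not mention the zero-inflation part. It does not say whether arm enters that part, or whether the two parts will be combined into an overall mean. The closing "Sample size" section identifies epilation as the intervention and surgery as the control.

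**The concern.** A zero-inflated Poisson model describes two things: whether an eye belongs to a class that always scores zero, and how many lashes are expected in eyes outside that class. A treatment may act on either. The plan describes one coefficient as the between-arm difference in log mean lash number, but the count-part coefficient compares the arms only among eyes outside the structural-zero class. An effect of treatment on the share of eyes with no lashes touching would be left out of it.

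That share matters here, because both treatments aim to leave no lashes in contact with the eye. A reader given the coefficient as the difference in means could conclude that the arms are alike when their average lash counts differ. The fault reaches the corneal count, which the plan treats as the clinically more relevant contact.

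**Working it through.** **The plan's figures.** The sentence on the coefficient carries no figure, and the documents give no zero-inflation probability or count mean. The design figure that bears on the comparison is the bold row of Table 1: 5% failing with surgery, 10% with epilation, margin 10%, 585 per arm, power 90%. It reproduces. SE = √[(0.05×0.95 + 0.10×0.90)/585] = √(0.1375/585) = 0.01533; (0.10 − 0.05)/0.01533 − 1.96 = 1.30; power = Φ(1.30) = 90.3%.

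**The identity.** Write π for the structural-zero probability, λ for the count mean in the remaining eyes, S for surgery and E for epilation.

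- Overall mean in an arm = (1 − π)λ.
- Difference in log overall means = log(λ_E/λ_S) + log[(1 − π_E)/(1 − π_S)].
- With arm in both parts, the count-part coefficient is the first term only. The quantity the plan names is the sum.

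The second term is zero if and only if π_E = π_S. With equal π and random effects distributed alike in both arms, a numerical check gave a log ratio of overall means of 0.500 against a coefficient of 0.500, so the plan's description is then right.

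**Size of the omitted term.** All π values are assumptions. It is 0 for equal π, log(0.25/0.20) = 0.22 for zeros of 80% v 75%, and log(0.30/0.10) = 1.10 for 90% v 70%.

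**The null case.** Take λ = 2 in both arms and π of 0.90 (surgery) and 0.70 (epilation). The overall means are 0.1×2 = 0.2 and 0.3×2 = 0.6, a ratio of 3.0. The coefficient is log(2/2) = 0.

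**Large-sample fits over assumed values (no random effect):**

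| π_S, λ_S | π_E, λ_E | Overall means S, E | True log ratio | Coefficient, arm in both parts | Coefficient, arm in count part only |
|---|---|---|---|---|---|
| 0.70, 2 | 0.70, 1.5 | 0.60, 0.45 | −0.288 | −0.288 | −0.288 |
| 0.80, 2 | 0.60, 2 | 0.40, 0.80 | +0.693 | 0 | +0.212 |
| 0.60, 2.5 | 0.80, 2 | 1.00, 0.40 | −0.916 | −0.223 | −0.424 |
| 0.60, 1.5 | 0.80, 2 | 0.60, 0.40 | −0.405 | +0.288 | +0.049 |
| 0.80, 3 | 0.60, 2 | 0.60, 0.80 | +0.288 | −0.405 | −0.304 |

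Row 1 is the equal-zeros case and agrees exactly. Rows 2 and 3 show a coefficient pulled towards the null, and rows 4 and 5 a reversed sign. Leaving arm out of the zero part does not cure the problem when π truly differs: the last column is still wrong in rows 2 to 5.

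**Do these settings fit the design?** Failure is 5 or more lashes. Under a plain Poisson count, P(5 or more) is 0.0527 for λ = 2. The null case therefore implies 0.1×0.0527 = 0.53% per visit with surgery and 0.3×0.0527 = 1.58% with epilation. That is the same direction as the design's 5% v 10%. The levels are not comparable, since the design figures cover any visit over two years.

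**The case against.** The strongest reply is that the plan's description can be correct. With arm in the count part only and equal zero inflation, the coefficient is the difference in log means, and the plan does not say that arm enters the zero part. Nor does it say that the zero part will go unreported. This stands: the fault is conditional, and a reader who concludes that one coefficient can never be the difference in log means goes too far. No statement in the documents says that treatment changes the structural-zero probability. Table 1 assumes different failure proportions in every row, but these could arise from the count part alone. The plan is still left relying on an unstated condition. It is a doubtful one when surgery is done once and epilation is repeated with possible non-adherence, as the "Primary analysis" section says.

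A reader might also infer that the coefficient is likely to favour the wrong arm. The documents do not support that. Take surgery with 80% zeros and λ = 2, and epilation with 50% zeros and λ = 1. The coefficient is log 0.5 = −0.69 while the mean ratio is 0.50/0.40 = 1.25. But this implies failure per visit of 0.2×0.0527 = 1.05% with surgery and 0.5×0.0037 = 0.18% with epilation, opposite to the design. The last row of the table has the same defect (3.7% v 2.1%). The row with epilation at 0.80 and 2 fits the design direction, but only by giving epilation more zeros than surgery.

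Finally, a reader might take the reference to all time points to mean that the baseline count and the 7-10 day count enter as outcomes. The documents do not say so. Trichiasis at baseline is tabulated with the baseline data, and the suture-removal visit is described separately under the surgical-arm outcome. The wording needs clarifying, no more.

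**Conclusion.** The point holds in conditional form. The coefficient is what the plan says it is only when zero inflation is equal in the two arms, and the plan does not state or defend that condition. If it fails, the reported log ratio is off by log[(1 − π_E)/(1 − π_S)] when arm is in both parts. Over the values tried above that runs from 0 to about 1.10, and it can hide a threefold difference in means. A wrong sign is mathematically possible, but nothing in the documents makes it probable.

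The algebra is certain. The sizes rest on assumed π and λ, with single-visit fits and no random effect. Two secondary outcomes are affected, the total and the corneal lash counts. The non-inferiority conclusion rests on a binary outcome with an exact interval and does not depend on this model. It should be corrected, but it does not threaten the trial's main result.

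**What to change.** Keep the random effects zero-inflated Poisson model, with these changes for both lash outcomes:

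- Enter arm in both the zero part and the count part, and report both effects with 95% confidence intervals.
- As the between-arm effect, report the ratio of overall mean lash counts, (1 − π)λ averaged over the random effects and covariates, with a delta-method or bootstrap interval (resampling participants). A marginalised zero-inflated model with random effects, which estimates this ratio directly, would serve equally well.
- Stay with a likelihood-based model. The "Censoring" paragraph removes participants once they fail, so whether later counts are missing depends on earlier ones. A correctly specified likelihood model allows for this under missing at random; an unweighted GEE generally does not.
- State that the outcome counts are those at 6, 12, 18 and 24 months, with the baseline count as a covariate.
- Reword the sentence on the coefficient to match.

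The cost is slightly more analysis work and a few lines of text. No new data are needed.

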**I certify that all the answers are accurately entered on the database_______ Date_________**

**Appendix C – Randomisation procedure**

**Randomisation trial 2**

**A. Preparing the master randomisation code**

- Each surgeon operating on patients in this trial will have their own separate randomisation sequence.
- Blocked randomisation codes to be generated by [name] using STATA
- The size of the blocks will vary at random.

1. Surgeon 1’s randomisation envelope sequence will be marked as follows E1/0001-E1/1000
2. Surgeon 2’s randomisation envelope sequence will be marked as follows E2/0001-E2/1000
3. Surgeon 3’s randomisation envelope sequence will be marked as follows E3/0001-E3/1000
4. Surgeon 4’s randomisation envelope sequence will be marked as follows E4/0001-E4/1000
5. Surgeon 5’s randomisation envelope sequence will be marked as follows E5/0001-E5/1000

[name] to keep one copy of the master code sheet. 2 further copies to be sent to people not involved in the trial for safe keeping.

A 4th copy to be sent to a person in Ethiopia independent of the trial for the preparation of the individual envelopes.

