Statistical analyses will calculate the difference in proportion failing in the two arms, and 95%CI for this difference using exact methods. Non-inferiority of epilation will be shown if the upper two-sided 95%CI around the estimated difference in proportions is below 10%. Blinded analyses conducted at the end of the trial showed an overall failure rate of 8%. Table 2 shows conclusions for different assumptions of the proportion failing in the surgery and epilation arm respectively. Given an overall failure rate of 8%, the conclusion will be that epilation is non-inferior to surgery if the proportion failing in the surgery arm is greater than 4.5%. Epilation will be deemed inferior, if the failure rate in the epilation arm is 15% or higher.

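### The acuity, entropion and conjunctivalisation comparisons name no baseline term, although the baseline values are recorded; this costs precision on secondary outcomes but not validity

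*Protocol*

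**What the plan says.** The Protocol carries its own Analytical Plan for Trial 2, and its Secondary outcomes section names a model for each of these comparisons.

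- Visual acuity: "The effect of the intervention on the visual acuity (logMAR score) at 12 and 24 months will be analysed by linear regression".
- Conjunctivalisation: "The effect of the intervention on the degree of conjunctivilisation at 24 months will be analysed by ordered logistic regression". Entropion at 24 months is given the same model.
- Patient satisfaction, where (b) is eye pain and (d) is watering: "Additionally the answers to questions (b) and (d) will be adjusted for baseline (pre-operative) response".

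The baseline values exist. In the Trial Recruitment Phase, acuity is measured and the eyelid examined before randomisation, and the baseline record form in Appendix B has logMAR, entropion grade and conjunctivalisation grade for each eye. The section on description of baseline data tabulates them by arm and checks for imbalance, but says nothing of what follows if imbalance is found.

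On surgeons, Appendix C says: "Each surgeon operating on patients in this trial will have their own separate randomisation sequence". The primary analysis (Primary outcome, d) reads: "Statistical analyses will calculate the difference in proportion failing in the two arms, and 95%CI for this difference using exact methods". Neither it nor the secondary Cox analysis mentions surgeon.

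**The concern.** Acuity and lid disease differ between patients before treatment starts. A comparison of follow-up values alone leaves all that variation in the error term, whereas a baseline covariate removes the part that persists. The plan's own footnote on acuity points this way: it calls acuity sensitive to cataract and ageing, and much of that would already be present at enrolment.

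Two things are at stake. First, acuity is an outcome patients notice, and an imprecise null result on it could be misread as showing that the arms are alike. Second, a plan that checks for imbalance without saying what it will do about it leaves the choice of covariates open until the data have been seen.

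**Working it through.** **1. The plan's own figure.** The sample size section says: "Our sample size of 1300 trial participants would provide 90% power to detect non-inferiority, assuming 10% loss to follow-up over 2 years". Table 1 uses a "sample size of 585 per arm (1300 recruited, 10% loss to follow-up"), with 5% failing under surgery, 10% under epilation and a 10-point margin.

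- Evaluable per arm: 1300 × 0.9 / 2 = 585.
- SE = √[(0.05×0.95 + 0.10×0.90)/585] = √(0.1375/585) = 0.01533.
- Power = Φ[(0.10 − 0.05)/0.01533 − 1.96] = 90.3%, against 90% stated.

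The figure reproduces. The 585 per arm is carried forward below; no size calculation is given for the secondary outcomes.

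**2. Visual acuity (linear model).** The baseline-to-follow-up correlation r is not in the documents, so 0.5 to 0.8 is an assumption. Working in SD units of follow-up logMAR, the unadjusted SE is √(2/585) = 0.0585. With the baseline covariate the variance is multiplied by 1 − r² and the interval width by √(1 − r²). The equivalent sample is 585/(1 − r²). The difference detectable with 90% power is (1.96 + 1.28) × SE. Power for an illustrative 0.15 SD difference is Φ(0.15/SE − 1.96).

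| r | Variance | CI width | Equivalent n per arm | Detectable difference (SD) | Power at 0.15 SD |
|---|---|---|---|---|---|
| unadjusted | ×1 | ×1 | 585 | 0.190 | 73% |
| 0.5 | ×0.75 | ×0.87 | 780 | 0.164 | 84% |
| 0.7 | ×0.51 | ×0.71 | 1147 | 0.135 | 95% |
| 0.8 | ×0.36 | ×0.60 | 1625 | 0.114 | 99% |

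**3. Lid grades (ordered logistic model).** The 1 − r² factor does not apply here. The odds ratio is non-collapsible, so adjustment changes the quantity estimated and the gain shows as power rather than as a smaller standard error. An illustrative simulation used 585 per arm, five ordered grades, a latent treatment shift of 0.15 SD and 150 data sets per setting:

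| Latent correlation (assumed) | Power without baseline | Power with baseline |
|---|---|---|
| 0 | 63% | 64% |
| 0.4 | 61% | 69% |
| 0.6 | 62% | 71% |

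Each figure has a simulation error of about √(0.62×0.38/150) = 4 points. Both models were fitted to the same data sets.

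**4. Surgeon strata on the primary.** Surgeons operate only in the surgery arm, so failure was allowed to vary by surgeon there (mean 5%, five equal strata) and held at 10% under epilation. Stratifying removes the between-surgeon variance from the 0.1375 in step 1.

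- Rates of 1, 3, 5, 7, 9%: between-surgeon variance 0.0008; ratio (0.1375 − 0.0008)/0.1375 = 0.994; power 90.5%.
- Rates of 0, 0, 5, 8, 12%: between-surgeon variance 0.00216; ratio 0.984; power 90.8%.

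Even the wider spread reduces the variance by only about 1.6% and adds half a point of power.

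**The case against.** The strongest reply is that naming a regression does not exclude covariates, that covariate lists are often left to a separate analysis plan, and that calling the baseline factors potential confounders suggests adjustment was in mind. Part of this stands: the unadjusted reading is an inference. But this document contains its own analytical plan, which says so where baseline adjustment is wanted. Silence three times beside one explicit statement reads most naturally as no adjustment.

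It is also fair that the correlation is assumed, and that new cataract or ageing over two years could lower it. At r = 0.3 the interval width would still be multiplied by √(1 − 0.09) = 0.95: a small gain, but not a loss.

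Four stronger readings are tempting, and the documents do not support them.

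- *That the comparisons are biased or the trial's conclusion is at risk.* Randomised comparisons without covariates are unbiased, and the primary outcome is not one of these three.
- *That baseline is ignored throughout.* Corneal opacity is analysed as change, pain and watering are adjusted, and baseline entropion and conjunctivalisation define the subgroups for failure.
- *That leaving surgeon out undermines the primary analysis.* The crude interval is at most slightly conservative. A stratified method would also replace the stated exact interval with an asymptotic one, on about 0.05 × 585 = 29 surgery-arm failures spread over up to five surgeons.
- *That the corneal opacity change analysis has the same fault.* If, as the footnote says, as few as 10% of patients have opacity at the outset, baseline grade is nearly constant and change equals the 24-month grade for the rest. No gain from remodelling it has been shown.

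**Conclusion.** The point holds as one of efficiency and clarity on three secondary outcomes. It is strongest for acuity, where the interval would be 13% to 40% narrower over the assumed correlations; that range assumes a linear relation of similar strength in both arms and 585 evaluable patients per arm. For entropion and conjunctivalisation the gain is modest, roughly 8 to 9 points of power in one simulated setting, and it brings a change of estimand that should be stated. For surgeon, the reason to act is to reflect how patients were randomised, not precision. Confidence is moderate on what the plan intends and high on the direction of the gain.

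**What to change.** In Secondary outcomes:

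- Add the trial eye's baseline logMAR as a covariate in the 12 and 24 month acuity regressions, using the same acuity measure (best corrected or pinhole) as the outcome.
- Add the matching baseline grade to the 24-month entropion and conjunctivalisation ordered logistic models, and say that the odds ratios are conditional on it.

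Optionally, stratify the secondary Cox model by surgeon; the envelope code logged on masterlist E2 identifies the surgeon's sequence in both arms. If a surgeon-stratified risk difference is wanted, list it as a sensitivity analysis and leave the exact primary interval unchanged.

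The cost is a few lines of wording. Every variable is already collected, and neither the sample size nor the primary analysis changes. The wording should be fixed before unblinding, since the plan already reports a blinded overall failure rate of 8%.

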**A: Trial Recruitment Phase (see diagram 1 below)**

1. **Identify locations (see diagram 2 below) for different parts of recruitment process**

Team Members who will perform this (appendix A)

SR (research fellow) and nurse 1 (examination nurse)

1. **Presentation to patients and accompanying people**

Team Members

Assistants 1 and 2 (consent field workers)

Procedure

- 1. Hand out project information sheets.
  2. Introduction re who we are.
  3. Info about what is known about trachoma.
  4. Info about what is not known about trachoma.
  5. Info about the trials.
  6. Info about safety to patient.
  7. Info about what we will do from now.

Late comers will receive similar presentation individually or in small groups.

1. **Triage Patient**

Team members

Field worker to call SR or EM to triage Patient to:

- 1. Trial 1 or trial 2
  2. Treatment for right eye/left eye/bilateral
  3. Decide which is trial eye if bilateral TT (using random eye table)

Procedure

1. Patients with trachomatous eye disease and no exclusion criteria, enter into study.
2. Patients with trachomatous eye disease and exclusion criteria. Do not enter into study, but give standard trachoma treatment, including surgery if required.
3. Patients with non-trachomatous eye disease:
   - 1. Emergency: to be seen by ophthalmologist or ophthalmological nurse and treated if necessary or arrangements made for urgent referral to local eye facility
     2. Non-emergency: to be seen by ophthalmological nurse and instructions for attendance at local eye unit with referral letter if required.

Inclusion criteria – trial 1

Patients with major trachomatous trichiasis (greater than 5 eyelashes touching the globe of either or both eyes), who consent to be part of the trial and do not have any of the exclusion criteria below.

Inclusion criteria – trial 2

Patients with minor trachomatous trichiasis (5 or less eyelashes touching the globe of either or both eyes), who consent to be part of the trial and do not have any of the exclusion criteria below.

Exclusion criteria for both trials

- Age less than 18 years
- Previous eyelid surgery
- Medically unfit, BP systolic >170, diastolic >110.
- Pregnant

1. **Consent**

Team Members

Assistants 1 and 2 (Consent field workers)

Procedure

- 1. Check if they heard initial lecture and if so whether they understood it.
  2. If not, then explain trachoma/trial.

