| - 1. Do you have any eye pain? | | 0 = No  1 = Yes |  | |  |
| - 1. If you do have eye pain, how often do you experience this? | | 0 = Never  1 = Once a week  2 = Once a day  3 = Several times a day  4 = Constantly |  | |  |
| - 1. Do you eyes water | | 0 = Never  1 = Occasionally  2 = Often |  | |  |
| - 1. During a typical day in the past week, how often did your eyes feel dry (so that you wanted to put water or other lubricant in them) | | 0 = Never 1 = Infrequently 2 = Frequently 3 = Constantly 4 = Not sure |  | |  |
| - 1. Do you epilate? | | 0 = No  1 = Yes |  | |  |
| - 1. How often do you epilate? | | 0 = Never  1 = More than once a week  2 = once/week to once/month  3 = Less than once a month |  | |  |
| - 1. When did you last epilate? | | 0 = Never  1 = Within last week  2 = 1 week to 1 month ago  3 = Greater than 1 month ago |  | |  |
| - 1. Who does the epilating? | | 0 = never  1 = You  2 = A friend or relative  3 = Health care worker |  | |  |
| - 1. What do you epilate with | | 0 = Don’t epilate  1 = Locally made forceps  2 = Machine made forceps  3 = Burning  4 = Cutting |  | |  |
| - 1. Has a health-worker previously told you that need eyelid surgery | | 0 = No  1 = Yes |  | |  |
| - 1. When was the last time you were offered surgery? | | 0 = Never  1 = Within last year  2 = >1 year ago |  | |  |
| - 1. If surgery has been recommended or offered to you in the past, but you have not received or accepted the surgery, what are your main reasons for this? *(list as many as appropriate)* | 0 = Never offered surgery (i.e. n/a) | | | *Yes No* | |
| 1 = No symptoms | | | *Yes No* | |
| 2 = Symptoms present, but didn’t know treatment needed | | | *Yes No* | |
| 3 = Cost | | | *Yes No* | |
| 4 = No one to accompany | | | *Yes No* | |
| 5 = Lack of time | | | *Yes No* | |
| 6 = Fear of the operation | | | *Yes No* | |
| 7 = Resistance of family | | | *Yes No* | |
| 8 = Transport difficulties | | | *Yes No* | |
| 9 = Don’t know where to get it | | | *Yes No* | |
| 10 = Other (specify reason) | | | *Yes No* | |
| Of the above reasons which is:   - 1. the most important*:* | |  | | | |
| - 1. the 2nd most important | |  | | | |

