**Studies on the Management of Trachomatous Trichiasis**

**Analytical Plan for Trial 2: Randomized controlled trial of immediate surgery vs. epilation for Minor Trichiasis**

**1. Participant flow**

*a) Eligibility, enrolment and follow-up*

The following will be shown by trial arm in a flowchart following CONSORT guidelines for non-inferiority trials (JAMA 2006: 295:1152-1160): Numbers eligible, consenting to take part, randomized, and who received the intended treatment. The numbers still in follow-up, censored, defaulting, and permanently lost-to-follow-up respectively at each visit will also be shown by arm. Reasons for declining to take part, not having surgery, or discontinuing follow-up will be summarized by arm.

*b) Censoring*

Patients in both arms will be considered as failures and immediately censored when they present with 5+ lashes in the trial eye. In addition, patients who present having had surgery (or repeat surgery) on the trial eye from other providers will be considered as failures and immediately censored.

1. **Description of baseline data**

The following characteristics of participants at baseline will be tabulated by arm:

- 1. Socio-demographic factors: age, sex, literacy, ethnic group.
  2. Behavioural factors: epilation habits, whether surgery has previously been offered, reasons for not having surgical treatment previously.
  3. Clinical status: trichiasis, entropion, inflammation, conjunctivilisation of lid margin, corneal scarring, evidence of epilation, visual acuity, symblepharon.

The distributions of these variables by treatment arm will be compared, to assess whether there is imbalance at baseline in these potential confounding factors.

1. **Primary outcome**

*a) Definition*

The primary outcome measure will be the proportion of participants with 5 or more lashes touching the eye on one or more follow-up visits. Lids with eyelash stubs which are not in contact with the eye will not be considered a treatment failure.

*b) Justification of primary outcome measure*

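### Satisfaction items (a) and (c) ask about change since treatment without fixing the same reference point in both arms

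*Protocol*

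**What the plan says.** In the Analytical Plan, under Secondary outcomes, Patient satisfaction, the items are introduced thus: "Patients are asked the following questions on the follow up questionnaires that indicate their satisfaction with the procedure". Item (a) reads "Do you think your vision is worse, the same or better than before your surgery or epilation". Item (c) asks patients with eye pain for the same three-way judgement against the same anchor. The plan then states: "The answers to each of these questions will be compared between the two arms of the trial at 12 months". It adds: "Additionally the answers to questions (b) and (d) will be adjusted for baseline (pre-operative) response".

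Three other places bear on what the anchor means:

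- The exclusion criteria for both trials list "Previous eyelid surgery". They do not list previous epilation.
- The baseline Ophthalmic Questionnaire in Appendix B asks "Do you epilate", how often, by whom and with what. It also asks "When did you last epilate", with answers running from never to more than a month ago. The form shown does not ask when epilation began.
- The Description of baseline data tabulates by arm "Behavioural factors: epilation habits" and clinical evidence of epilation.

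**The concern.** A change question compared between randomised arms needs one reference date for everyone. Here the anchor is the treatment itself, and the two treatments differ in how clearly they are dated. Surgery is a single event, and a patient with earlier lid surgery cannot enter. Epilation is a habit that many participants may have had before the trial, and the plan prepares to record it.

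If existing epilators in the epilation arm look back further than patients in the surgery arm, the arms differ in the period judged as well as in treatment. For vision, a longer period takes in more change from causes unrelated to allocation; the plan itself names cataract and ageing as such causes. For pain, the earlier anchor may be untreated trichiasis, which could make epilation look better. The two items could therefore be pushed in opposite directions.

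**Working it through.** **Reading the anchor for each group of participants**

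| Baseline history | Allocated to surgery | Allocated to epilation |
|---|---|---|
| Never epilated | Trial operation (or later epilation, if surgery fails and the patient starts) | Start of trial epilation |
| Existing or former epilator | Trial operation, or first epilation | Start of trial epilation, or first epilation |

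Only the second row is open, and it is open in both arms. Randomisation puts a similar share of such patients in each arm. What matters is whether they choose the earlier anchor more often in one arm. A patient in the surgery arm has a distinct, dated operation to refer to. A patient continuing an old habit may have a weaker marker, although the trial does give epilation training and a forceps pack.

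**Size**

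The plan gives no figure to reproduce for these items. Let:

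- f = share of each arm that epilated before enrolment,
- m_E and m_S = share of those using the earlier anchor in the epilation and surgery arms,
- d = increase in the probability of answering *worse* caused by the longer look-back.

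With no true treatment effect, the false difference is f × (m_E − m_S) × d.

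The documents give none of f, m_E, m_S or d. For illustration I assume 10% *worse* over 12 months and 20% over the longer period, so d = 0.10. I take 585 per arm from the plan's Table 1. The false-positive rate is that of a two-sided 5% z-test with unpooled variance.

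| f | m_E | m_S | *Worse*, surgery arm | *Worse*, epilation arm | False difference (points) | False-positive rate |
|---|---|---|---|---|---|---|
| 0.5 | 0.5 | 0 | 10.0% | 12.5% | 2.5 | 27% |
| 0.5 | 0.5 | 0.25 | 11.25% | 12.5% | 1.25 | 10% |
| 0.5 | 0.5 | 0.5 | 12.5% | 12.5% | 0 | 5% |
| 0.8 | 0.5 | 0 | 10.0% | 14.0% | 4.0 | 56% |
| 0.8 | 0.5 | 0.25 | 12.0% | 14.0% | 2.0 | 17% |
| 0.8 | 0.5 | 0.5 | 14.0% | 14.0% | 0 | 5% |

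Worked line (second row): 0.5 × (0.5 − 0.25) × 0.10 = 0.0125. The standard error is √[(0.1125 × 0.8875 + 0.125 × 0.875)/585] = 0.0189, and 0.0125/0.0189 = 0.66, which gives a rejection rate of about 10%.

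The result turns on m_E − m_S. Setting m_S to zero, as in rows 1 and 4, is the least favourable choice and is hard to defend, because existing epilators allocated to surgery hear the same words.

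**The case against.** The strongest reply is that the trial treatment is plainly what was meant. The lead-in speaks of satisfaction with the procedure, the wording pairs the two trial treatments, and the plan calls the baseline response pre-operative. Trial epilation also begins with an identifiable event, the training session. This stands as evidence of intent. It does not settle how a patient already epilating hears the question, because the lead-in belongs to the analysis plan and is not part of the item.

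The follow-up questionnaire and any interviewer instructions are not in the text available, so a clarifying prompt cannot be ruled out. That also stands, and it is one reason for the low priority.

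A reader might infer three stronger things that the documents do not support:

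- *That the arms are in fact compared over different periods, with the epilation arm looking back years.* No passage says so. The baseline form shown records how recently patients epilated, not for how long, and the problem arises only for those who take the earlier reading.
- *That the false-positive rate is known to be high.* The large values need assumed inputs and little or no early anchoring in the surgery arm. With equal early anchoring in both arms the rate stays at 5%.
- *That leaving (a) and (c) without baseline adjustment is an error.* Items (b) and (d) have a counterpart on the baseline form. Items (a) and (c) ask about change, so there is no baseline response to adjust for.

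**Conclusion.** The wording of (a) and (c) does not fix the same reference point in both arms. It normally points to the trial operation for surgery, and it is open for anyone who epilated before enrolment. A biased comparison follows only if existing epilators take the earlier anchor more often in the epilation arm than in the surgery arm. That is plausible but undocumented. Neither the size nor the net direction can be derived from the documents; the figures above show only how both depend on the assumptions.

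The reach is narrow: two items within one secondary outcome. The primary outcome, the sample size and the non-inferiority conclusion do not depend on them. Vision is also measured as logMAR acuity, compared at 12 and 24 months, and pain by the baseline-adjusted item (b). Minor priority.

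**What to change.** Anchor (a) and (c) to the enrolment visit in both arms, for example *than on the day you joined this study*. This costs one change of wording on the follow-up questionnaire.

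For answers already collected with the present wording, keep the full between-arm comparison and add a sensitivity analysis of (a) and (c) stratified by baseline epilation history. Define the clean stratum by the answer Never to "When did you last epilate": for these patients the anchor can only be the trial treatment or something later. The answer No to "Do you epilate" is less suitable because it asks about current practice, so former epilators can fall into it. The stratifier is recorded before randomisation, so the comparison within each stratum remains randomised. The cost is lower precision in the never-epilated subset, whose size the documents do not give. For that reason, and because it covers only part of the trial population, it should not replace the full comparison.
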